## Methods

### Study setting

This single centre study will take place at the Plastic, Reconstructive and Hand Surgery Department of the Jeroen Bosch Hospital,’s-Hertogenbosch, the Netherlands.

### Eligibility criteria

#### Inclusion criteria

All eligible participants have to meet all of the following criteria:-Complaints of idiopathic ulnar nerve entrapment at elbow, objectified clinically, with an electrophysiologic confirmed (EMG) diagnosis;-Ability to measure the outcome of the study in this patient (e.g. life expectancy > 1 year, no planned relocation);-Ability to speak and understand Dutch;-Informed consent (written)

#### Exclusion criteria

A potential subject who meets any of the following criteria will be excluded:- Age under 18;- Not able to provide informed consent;- Previous surgical cubital tunnel release or other surgery performed in the same elbow;- Subluxation palpable during elbow flexion pre-operatively or occurring during surgery after release for which a transposition of the ulnar nerve is needed.

### Intervention

Patients will be randomized for the open cubital tunnel release or endoscopic cubital tunnel release. Both interventions are standard of care in the Jeroen Bosch Hospital. Patients who undergo a cubital tunnel release receive plexus or general anesthesia depending on the preference of the patient. After applying a pneumatic tourniquet, a longitudinal incision is made between the medial humeral epicondyle and the olecranon. The ulnar nerve is identified and released proximally and distally. The nerve branches of the flexor carpi ulnaris are identified. After wound closure with a resolvable suture, the patient receives a pressure bandage in a 45 degrees flexion and the bloodless field is abolished. Both the open and endoscopic release are performed in the same manner, except the length of the incision which is smaller in the endoscopic release; after identification of the ulnar nerve, the endoscope is inserted and the nerve is released with use of the endoscope. The HOPKINS ® Telescope 30° (4 mm, 18 cm) by Karl Storz. In addition, patients can watch the nerve release during the operation or after the surgery.

Both patient groups receive the same aftercare. After two days, the pressure bandage can be taken off and full active mobilization of the elbow is allowed. After two weeks full use of the arm (work, sport and axial load) is allowed. Patients can take acetaminophen postoperatively. We do not recommend physiotherapy.

#### Blinding

Patients, doctors and researchers will not be blinded for the treatment allocation. The nature of our study does not allow for blinding of the aforementioned parties. Unblinding does therefore not apply.

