### Statistical methods

#### Primary study parameter

Difference in change in BCTQ: Linear generalized estimating equation (GEE) analyses will be used to study the longitudinal relationship between treatment group (determinant) on the one hand, and BCTQ score (outcome variable) on the other hand. This will be performed for the different domains of the BCTQ. This results in a single regression coefficient representing the population average difference in the outcome variable over time that incorporates between-subject and within-subject correlations.

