#### Secondary study parameters

- Difference in change in PRUNE: Linear generalized estimating equation (GEE) analyses will be used to study the longitudinal relationship between treatment group (determinant) on the one hand, and BCTQ score (outcome variable) on the other hand. This will be done for the different domains of the PRUNE.- Difference in PREM vs change in PROM: The PREM score is a continuous outcome and will be analyzed using an independent T-test if distributed normally and a Mann–Whitney U test when not. The change in PROM (BCTQ) score is a continuous outcome and will be analyzed using a paired T- test if distributed normally and a Wilcoxon signed rank test when not. To assess the association between PREM scores and PROM change scores, linear regression analyses will be performed. Multivariable regression models will be used to adjust for potential confounding of various patient and disease characteristics, including age, sex, body mass index, smoking and duration of disease. All domains of the PREM (pre-, intra- and postoperative care and communication) were introduced simultaneously in the same model as independent to determine to what extent the variation in treatment outcome between patients could be explained by the experience with health care, as measured by the PREM. The outcome is measured by the beta-coefficient, showing the change in PROM associated with 1 absolute point increase in PREM subscale.- Sensibility: Sensibility is measured using two-point discrimination, resulting in a categorical outcome. The outcome includes > 2 categories and will be compared using a Chi-Squared test.- RTW, Complications, Scar Aesthetics: Return of full function in days, number of complications and scar aesthetics are continuous outcomes and will be analyzed using an independent T-test.- Correlation between VAS, Bishop, two-point discrimination and both PROMs: The association between VAS score, Bishop score, two-point discrimination and PROMs (both BCTQ and PRUNE) will be determined using the Pearson or Spearman correlation, depending on the data distribution. Analyses will be performed in two dimensions: 1) the correlation between preoperative VAS score, Bishop score, two-point discrimination and both PROMs and 2) the association between change in VAS score, Bishop score, two-point discrimination and both PROMs (12-month score minus preoperative score).

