#### Analysis plan

Descriptive statistics will be provided using mean with standard deviation (SD), median with interquartile range (IQR) or frequencies/percentages depending on the type of distribution of the data. Distribution of data will be assessed using histograms and skewing.

Values of *p* < 0.05 will considered statistically significant. All analysis will be on an intention- to-treat basis. We will correct for multiple testing, *P*-values will be corrected by the Bonferroni method [21].

For exclusion and dropout, numbers and reasons are reported to ensure internal validity. A flow- chart will show the number of patients lost during follow-up including reasons for the loss of follow-up. An analysis on basic characteristics will be performed to control for selection bias. Missing values will be imputed using multiple imputations when meeting the assumption of missing completely at random/missing at random (MCAR/MAR), as imputation will always increase precision and often also reduce bias [22, 23].

Table 1 shows the variables at each study visit.

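### The protocol declares blinding impossible for all researchers, but its reason does not reach an analyst working on coded questionnaire data

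*Protocol article*

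**What the plan says.** The Blinding section of the protocol article reads: "Patients, doctors and researchers will not be blinded for the treatment allocation". It then gives the reason: "The nature of our study does not allow for blinding of the aforementioned parties". The section closes by treating unblinding as not applicable. No analyst is mentioned separately, and the article does not say who will analyse the data.

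The Objectives section states a directional hypothesis: endoscopic release is expected to do better on primary and secondary outcomes alike.

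Three statements leave analysis decisions until the data have been inspected:

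- Analysis plan, on distributions: "Distribution of data will be assessed using histograms and skewing". No numeric rule is given.
- Analysis plan, on missing data: "Missing values will be imputed using multiple imputations when meeting the assumption" of data missing completely at random or at random.
- Secondary study parameters, on the PREM score: "will be analyzed using an independent T-test if distributed normally and a Mann–Whitney U test when not".

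**The concern.** The protocol is not silent about blinding the research team. It rules blinding out, on a ground that belongs to the operation and not to the analysis. Surgeons must know what they do, and patients may see the incision or watch the release. Neither fact obliges the person who fits a GEE to questionnaire scores to know which label stands for endoscopic release.

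Patients report the primary outcome knowing their treatment, so analysis is one of the few stages that can still be protected. Where a judgement is left open and the team expects one arm to do better, visible labels allow that expectation to influence the judgement. What is at stake is the credibility of the imputation decision for the primary BCTQ result and of the test chosen for the PREM comparison.

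**Working it through.** The plan gives no figure on this point, so the check is mainly a comparison of sections.

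**Step 1. Whom does the stated reason fit?** It fits the operating surgeon, and the protocol extends it to patients. For an analyst, the described set-up points the other way. Data are held in REDCap under a unique patient code (Data collection section), and the REDCap administrator made the allocation sequence (Sequence generation section). An export with arms labelled A and B is therefore feasible. One obstacle is real: the Intervention section says the incision is shorter in the endoscopic arm. Incision length would reveal the arm, and operation time and decompression length may do so too.

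**Step 2. Which analysis choices are open, and do they affect a between-arm result?**

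| Choice | Status in the protocol | Between-arm result? | Reaches the primary outcome? |
|---|---|---|---|
| Model for BCTQ and PRUNE | Linear GEE, fixed | Yes | BCTQ yes, but no switch |
| Whether to impute | Depends on a judgement about missingness | Yes | Yes |
| PREM: t-test or Mann–Whitney | Depends on a judgement of normality | Yes | No |
| PROM change: paired t-test or Wilcoxon | Depends on a judgement of normality | No, within patient | No |
| Pearson or Spearman | Depends on the distribution | No, association between measures | No |
| Covariates in the PREM–PROM regression | Named list, not fully closed | No | No |
| Sensibility, return to function, complications, scar | Chi-squared or t-test, fixed | Yes | No |
| Surgical characteristics | t-test or Fisher, fixed | Yes | No |

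Two choices are both open and between-arm: imputation and the PREM test. Imputation matters more. Data missing at random cannot be confirmed from the observed data, so the condition is a judgement, and it bears on the BCTQ analysis.

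**Step 3. Can an error-rate cost be assigned to the lack of masking?** Take 72 patients per arm (144 / 2, from the sample-size section), no true difference, and an analyst who reports the smaller of the two-sided t-test and Mann–Whitney p-values. The distributions are assumptions; the protocol gives none for the PREM.

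| Assumed data | t-test | Mann–Whitney | Smaller p |
|---|---|---|---|
| Normal, 10,000 trials | 4.9% | 4.9% | 5.8% |
| Lognormal, 10,000 trials | 4.3% | 5.0% | 7.3% |
| Another skewed score, 8,000 trials | 5.2% | 5.1% | 6.7% |

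Now swap the labels A and B. The t statistic changes sign, so its absolute value and two-sided p-value stay the same. The Mann–Whitney statistic U becomes 72 × 72 − U = 5,184 − U. Its distance from the centre, 5,184 / 2 = 2,592, is unchanged, and so is its p-value. An analyst with coded arms could still compute both and report the smaller, with the same rates. The excess over 5% is the price of an unfixed test-choice rule. None of it measures the absence of masking.

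What coding does remove is the ability to steer a judgement towards a known arm. The documents give no basis for putting a number on that.

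**The case against.** Several objections carry weight.

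- **Who decides, and what they know.** A reader might infer that every data-dependent decision will be taken by people who see which arm benefits. The article does not say so. It does not name the analyst or say when decisions are taken, it excludes interim analyses, and knowing allocation is not the same as having seen results. This objection stands; the documents support only that such decisions could be made with labels visible.
- **Size.** A reader might also take the 6.7% error rate as the cost of unmasked analysis. Step 3 shows that it is not. It also assumes an analyst who chooses by p-value, whereas the protocol makes the choice depend on normality. This stands in full.
- **Breadth.** The correlation choice ("will be determined using the Pearson or Spearman correlation, depending on the data distribution"), the paired test and the covariate list are not arm comparisons as the statistical section describes them, although the Secondary outcomes section does allow for a difference in correlation. This stands, and it narrows the point to two judgements.
- **An unseen SAP.** Coded exports and locked decision rules often sit there, so their absence from an article is no fault. This stands for the operational detail but does not answer the main point: the article declares blinding of researchers impossible, and an SAP that masked the analyst would contradict it.
- **Larger bias elsewhere.** Masking the analyst does nothing about unblinded patients scoring their own BCTQ. True, but that is no reason to leave the analysis stage unprotected.

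**Conclusion.** The concern holds in a limited form. The reason given for leaving researchers unblinded does not cover a person analysing coded BCTQ, PRUNE and PREM data, so the statement is broader than its justification. Two open judgements that affect between-arm results are exposed: the imputation decision, which reaches the primary outcome, and the PREM test, which is secondary. The linear GEE and most other tests are already fixed.

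The effect on bias is not quantifiable from the documents, and no rise in the false-positive rate should be attributed to the lack of masking. Sample size, alpha and power are unaffected. The conclusion assumes that whoever analyses the data falls under the protocol's term for researchers, and that no unseen document already fixes the two judgements. This is a modest, inexpensive improvement to a stated rule and does not by itself threaten the trial's conclusions.

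**What to change.** 1. In the Blinding section, limit the impossibility statement to the people it fits, and say that the analyst works on an export with arms coded A and B.
2. Withhold incision length, decompression length and operation time from that export.
3. Lock and date the imputation decision, the PREM test choice and the primary GEE output before the code is broken.
4. Run the surgical-characteristics comparisons afterwards, on the full data.

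The cost is low but not zero. The withheld variables are planned outcomes, so data release and analysis happen in two stages, with a coded export and a short dated lock note. No change to patient procedures is needed. Coding the arms does not by itself stop a free choice between tests; locking the PREM choice in step 3 is what does that.

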### Outcomes

#### Primary outcome

The difference in change (Δ, preoperatively and postoperatively) in BCTQ score between both treatment groups at 3, 6 and 12 and 18 months follow-up.

#### Secondary outcomes

- The difference in change (Δ, preoperatively and postoperatively) in PRUNE score between both treatment groups at 3, 6, 12 and 18 months follow-up;- The difference in PREM between both treatment groups at 3 months follow-up and its effect on the change (Δ, preoperatively and postoperatively) in PROM;- The difference in post-operative recovery of sensibility between both treatment groups at 3, 6 and 12 months follow-up;- The difference in time until return of full function (RTW) in days between both treatment groups;- The difference amount of complications between both treatment groups during the follow-up period of 18 months;- The difference in scar aesthetics between both treatment groups at 12 months follow-up;- The (difference in) correlation between VAS score (0-10, 0 being no pain to 10 being the worst pain), Bishop score (a 5 point scale, resulting in a total score of poor 0-2, fair 3-4, good 5-7, excellent 8-9) [16], two-point discrimination and both PROMs (BCTQ and PRUNE) at 3, 12 and 18 months follow-up;- The difference in surgical characteristics (duration of procedure, length of incision, amount of peroperative subluxation of the nerve after release) between both treatment groups.

#### Other parameters

In addition, disease characteristics (including affected side, duration of symptoms, the Tinel sign (positive or negative), handedness, use of splints, physiotherapy, avoidance of triggering factors and the McGowan classification) and demographic characteristics (including sex, age, type of work, smoking) will be collected. The McGowan classification is a three point scale assessing senbility and motor deficit: 1 Subjective symptoms, hypoesthesia; 2 Loss of sensibility, weakness of intrinsic musculature and or light muscle wasting and 3 Severe deficit of sensibility and motor functions.

### Follow-up

The follow-up takes 18 months post-operation. The schedule of trial enrolment is shown in Table 1. Study visits take place at 2 weeks, 3 months and 12 months post-operative with a surgeon or resident. These visits are standard of care. At 6 weeks follow-up, a phone consultation will be scheduled with a surgeon or resident. At 18 months patients will be asked to fill in questionnaires at home. These last two follow-up moments are additional to standard follow-up.

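### Outcomes are set at time points for which the described follow-up has no suitable contact: 6 months for BCTQ, PRUNE and sensibility, and 18 months for two-point discrimination

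*Protocol article*

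**What the plan says.** All references are to the protocol article.

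**What is to be measured, and when.** Under Primary outcome, the comparison is of change "in BCTQ score between both treatment groups at 3, 6 and 12 and 18 months follow-up". Secondary outcomes sets the PRUNE comparison "in PRUNE score between both treatment groups at 3, 6, 12 and 18 months follow-up" and also lists: "The difference in post-operative recovery of sensibility between both treatment groups at 3, 6 and 12 months follow-up". A further secondary outcome correlates VAS, Bishop score, "two-point discrimination and both PROMs (BCTQ and PRUNE) at 3, 12 and 18 months follow-up".

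**How sensibility is measured.** Secondary study parameters states: "Sensibility is measured using two-point discrimination, resulting in a categorical outcome".

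**What contacts are described.** Follow-up states: "Study visits take place at 2 weeks, 3 months and 12 months post-operative with a surgeon or resident". It continues: "At 6 weeks follow-up, a phone consultation will be scheduled with a surgeon or resident". Then: "At 18 months patients will be asked to fill in questionnaires at home". The call and the 18-month questionnaires are described as extra to the usual follow-up. The section refers to Table 1 for the schedule, but that table is not visible in the text available.

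**What is analysed.** For the correlation outcome, Secondary study parameters describes two analyses: one on preoperative values, and one on change from the preoperative value to 12 months.

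**The concern.** A time point in an outcome definition needs an occasion on which the measurement can be made. Here three outcomes, one of them primary, name 6 months, and the Follow-up text gives no contact then. Separately, a test done by an examiner is wanted at 18 months, when patients only complete forms at home.

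If staff work from the Follow-up text, the 6-month measurements are not taken and cannot be recovered later. The multiple imputation foreseen in the Analysis plan would not help, because no patient would have an observed 6-month value from which to build the imputation model. The primary GEE analysis yields one coefficient averaged over the measurement times, so including or omitting 6 months also changes what that coefficient averages. For sensibility, one of three planned comparisons would disappear.

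**Working it through.** **Step 1. Outcome time points against described contacts**

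| Time | Outcomes set there | Contact described in Follow-up | Obtainable? |
|---|---|---|---|
| 6 weeks | none | telephone call | not applicable |
| 3 months | BCTQ, PRUNE, sensibility, correlations | visit | yes |
| 6 months | BCTQ, PRUNE, sensibility | none | not as described |
| 12 months | BCTQ, PRUNE, sensibility, correlations | visit | yes |
| 18 months | BCTQ, PRUNE, correlations (VAS, Bishop, two-point discrimination) | home questionnaires | questionnaire items yes; two-point discrimination no |

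The 3- and 12-month rows agree. The 6- and 18-month rows do not.

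**Step 2. Could the 6-month gap be a slip or an omission?** There are two benign explanations.

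- The 6-week call may be meant as a 6-month call. No outcome is set at 6 weeks, which makes this plausible.
- Table 1 may list a 6-month questionnaire.

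Either could supply BCTQ and PRUNE. Neither a call nor a form can supply two-point discrimination, the only measure of sensibility named. The section on data collection gives two sources, the medical chart and patient questionnaires. Without a visit there is no chart entry for this test. So 6-month sensibility and 18-month two-point discrimination remain unobtainable under both explanations.

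**Step 3. Correlation outcome against its analysis.** Secondary outcomes sets 3, 12 and 18 months. Secondary study parameters analyses preoperative values and the 12-month change. The 3- and 18-month correlations therefore have a stated time point but no stated analysis.

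**Step 4. What losing 6 months would do to the primary comparison.** The protocol gives SD 0.7, 144 evaluable patients (72 per arm at 1:1) and α = 0.05. It does not state the correlation ρ between repeated measures, the number of measurements T, the difference chosen or the sidedness. The following are therefore assumptions: difference d = 0.3 (the smallest of the listed minimal important changes), two-sided test, equal correlation between occasions, and ρ from 0.5 to 0.79.

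Formulas: SE² = 2·SD²·[1 + (T − 1)ρ] / (T·n), and power = Φ(d/SE − 1.96).

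The plan's figure first: with T = 4 and ρ = 0.79, n per arm = 2(1.96 + 0.8416)² × 0.49 / 0.09 × (1 + 3 × 0.79)/4 ≈ 85.5 × 0.8425 ≈ 72, a total of 144; and 144/0.90 = 160. The value 0.79 was solved for so as to return 144. It shows that the formula can reach the stated number, not that the authors used this value.

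| ρ (assumed) | T | [1 + (T − 1)ρ]/T | SE | d/SE | Power |
|---|---|---|---|---|---|
| 0.79 | 4 | 0.8425 | 0.1071 | 2.80 | 0.800 |
| 0.79 | 3 | 0.8600 | 0.1082 | 2.77 | 0.792 |
| 0.50 | 4 | 0.6250 | 0.0922 | 3.25 | 0.902 |
| 0.50 | 3 | 0.6667 | 0.0953 | 3.15 | 0.883 |

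Dropping one of four occasions costs 0.8 percentage points of power at ρ = 0.79 and 1.9 at ρ = 0.5.

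**The case against.** The strongest reply is that the deciding evidence is out of sight. Follow-up defers to Table 1, and the Analysis plan says the table gives the variables per visit. The prose does not claim to be exhaustive: it says the call and the 18-month questionnaires are additional, not that they are the only additions. BCTQ and PRUNE need no visit, and home completion is already used at 18 months. The primary coefficient can be estimated without 6 months at little cost in power.

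Much of this stands, and it rules out several stronger readings that a reader might infer:

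- *That 6-month primary data will be missing for every patient.* This would follow only if Table 1 also lacks a 6-month questionnaire, which cannot be seen.
- *That the primary outcome could not be reported.* The GEE coefficient remains estimable from 3, 12 and 18 months; what would be lost is the 6-month contribution.
- *That all 18-month correlations fail.* VAS, BCTQ and PRUNE can be self-reported, so correlations among them could survive if VAS is on the home form.
- *That the Bishop score cannot be obtained at 18 months.* The article gives its score bands but not its items or who scores them, so this cannot be judged.

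The reply does not reach two-point discrimination. Only examinations at 6 and 18 months would supply it. If Table 1 listed them, it would conflict with the Follow-up text, which names in-person visits only at 2 weeks, 3 months and 12 months and describes 18 months as home completion. Nor is this detail that an article may leave to a fuller document: it states both the outcome times and the contacts, and they disagree.

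**Conclusion.** The outcome time points and the described follow-up cannot both hold, and the text needs correcting on any reading of Table 1. The certain loss, if Follow-up is applied as written, is to secondary examination outcomes: one of three sensibility time points (6 months) and the 18-month correlations that involve two-point discrimination. Loss of 6-month BCTQ and PRUNE data is possible but depends on Table 1. If 6 months were dropped from the primary outcome, the power cost would be about 1 to 2 percentage points, conditional on the assumed difference, correlation range, number of occasions and sidedness. The issue is therefore chiefly whether the stated outcomes can be ascertained, and only marginally one of power. The mismatch between the correlation outcome's time points and its analysis is a smaller inconsistency to settle at the same time.

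**What to change.** Reconcile Primary outcome, Secondary outcomes, Follow-up, Secondary study parameters and Table 1:

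1. **BCTQ and PRUNE at 6 months.** Describe a 6-month home questionnaire in Follow-up, in the same mode as at 18 months; or delete 6 months from both outcomes and say that the primary coefficient averages over 3, 12 and 18 months. Confirm whether the 6-week call is meant as written.
2. **Sensibility.** Delete 6 months, leaving 3 and 12 months, where visits exist.
3. **Correlations.** Confine those using two-point discrimination to preoperative, 3 and 12 months. State how the Bishop score is obtained if it is kept at 18 months. Make the outcome definition and the analysis name the same time points.
4. **Sample size.** State the number of measurements, correlation and difference used, so that the calculation matches the schedule finally adopted.

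The cost is at most one extra home questionnaire per patient, with no additional visit. The change should be made before patients reach 6 months, since measurements missed then cannot be collected afterwards.
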